#### 5.10.4.3 Additional Analyses - Subgroup

Planned subgroup analyses will be conducted to investigate possible interactions between treatment effects and whether or not surgery was required on both eyes, with separate estimates and confidence intervals being reported for such patients. We will also investigate a possible interaction between treatment effect and trial site as a pre-specified subgroup analysis.

### 5.10.5 Analysis Population and Missing Data

While there is no planned research visit between surgery and the postoperative visit at 3 months, it is likely that patients will attend standard NHS visits following surgery. Visual acuity data will therefore be extracted from patient records for all patients and used in the multiple imputation model for the primary outcome for patients who do not attend for 3 months follow-up.

Missing data will be dealt with using multiple imputation by chained equations. Results will be combined using Rubin’s rules. Data will be assumed to be missing at random (MAR), in essence the data available for patients before they drop out will be used to predict the endpoint. The imputation will be performed following a pre-specified procedure and conducted separately by trial group. Reasons for missingness may be important and these will be investigated using logistic regression of covariates on an indicator of missingness. Sensitivity analysis will investigate the validity of the missing at random assumption.

### 5.10.6 Economic evaluation

We will undertake a detailed analysis of the costs and the cost-utility of laser assisted phacoemulsification cataract surgery compared with manual phacoemulsification cataract surgery (standard care). The analyses will conform to accepted economic evaluation methods (eg NICE methods guidance). All costs will be assessed from the perspective of the NHS and personal social services. We will estimate cost and cost-utility a) for the ‘within-trial’ period, based on the clinical and health related quality of life results at baseline and follow-up, and b) over the expected lifetime of the patients. We have selected the EQ-5DV as the most appropriate instrument for use in this population.

#### 5.10.6.1 Within-trial analysis

The units of outcome for the within-trial cost-effectiveness analyses will be the incremental cost per unit change in the uncorrected distance visual acuity (UCVA) in the study eye and the incremental cost per quality-adjusted life year (QALY) gained. QALYs will be calculated based on the responses to the EQ-5D-3L+vision bolt-on question (EQ-5DV) collected at baseline and follow-up. Patient-specific utility profiles will be constructed assuming a linear change in utility values measured using the EQ-5DV questionnaire at baseline and six week, three month, six month and 12 month follow-up time points. Utility estimates will be calculated according to the area under the curve approach, adjusting for baseline differences in patients in the trial arms if necessary. Missing EQ-5DV and resource use data will be addressed using appropriate statistical methods in consultation with the trial statistician.

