## 5.6 Participant Timeline

**Figure 1: Schedule of Assessments**

|  | Standard pre-assessment (for study and non-study patients) | **Baseline** | **Randomisation** | **Follow up** | | | | |
| --- | --- | --- | --- | --- | --- | --- | --- | --- |
|  |  | Surgical Pre Assessment Visit | Randomisation and surgery | Standard non-study post-op appt | 6 weeks post-surgery (by post)  (ideally +/-14 days) | 1^st^ trial apt: 3 months post-surgery  (ideally +/-14  days) | 6 months post-surgery  (by post)  (ideally+/-14  days) | 2^nd^ trial apt: 12 months post-surgery  (ideally +/-14 days) |
| Visit Number | *1* | *1 or later* | 2 | *3* |  | *4* |  | *5* |
| Past medical and ocular history | X | X |  |  |  |  |  |  |
| Consent for cataract surgery | X |  |  |  |  |  |  |  |
| Informed Consent & eligibility screening |  | X |  |  |  |  |  |  |
| Identification of study eye |  | X |  |  |  |  |  |  |
| Visual acuity: UDVA, pinhole, +/- glasses (Snellen), each eye | X |  |  | X |  |  |  |  |
| Visual Acuity: UDVA^1^ & CDVA^2^ (logMAR) each eye and binocular |  |  |  |  |  | X |  | X |
| Visual acuity (LogMAR) with usual method of correction |  |  | X^7^ |  |  |  |  |  |
| Subjective refraction |  |  |  |  |  | X |  | X |
| Ocular biometry | X |  |  |  |  |  |  |  |
| Pentacam corneal topography | X^6^ | X |  |  |  | X |  | X |
| Optical coherence tomography (OCT)^3^ | X^6^ | X^8^ |  | X^6^ |  | X |  | X |
| Inclusion/Exclusion Criteria |  | X |  |  |  |  |  |  |
| Catquest-9SF questionnaire |  | X |  |  | X | X | X | X |
| EQ-5D-3L+vision bolt-on question (EQ-5DV) |  | X |  |  | X | X | X | X |
| CSRI^5^ |  | X |  |  |  | X | X | X |
| Endothelial cell count measurement | X^6^ | X^8^ |  |  |  | X |  | X |
| Surgery |  |  | X |  |  |  |  |  |
| Adverse Event Collection |  |  |  |  | X | X | X^4^ | X |

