## 5.9 Assignment of Intervention

### 5.9.1 Allocation

#### 5.9.1.1 Sequence generation

Patients will be randomised in a 1:1 ratio to either surgical procedure via the Sealed Envelope.com website. Sealed Envelope is a randomisation service provider that provides a proven, reliable and centralised randomisation system. The system will be custom designed to the trial requirements.

This will use minimisation with a random element with stratification by a) treatment centre, b) surgeon, and c) whether in the local clinician’s opinion, the patient will require surgery on one or both eyes.

A random trial arm allocation will be computer generated. Sealed Envelope will provide the randomised treatment for each participant.

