#### 5.10.4.2 Statistical Methods – Outcomes

The primary outcome is uncorrected distance visual acuity at 3 months following surgery on the study eye, measured using an ETDRS chart at a starting distance of 4 metres. Mean UDVA will be reported together with a two-sided 95% confidence interval. This will be compared between treatment groups using regression analysis adjusting for baseline habitual logMar^[[1]](#footnote-2)^ visual acuity and the randomisation stratifiers (treatment centre, surgeon, and whether or not patients have one or both eyes eligible). We will include trial site in our regression models as a fixed effect and surgeon as a random effect. If the upper end of the 95% CI for the difference between means does not cross the non-inferiority limit of 0.1 logMAR, then laser surgery will be regarded as non-inferior. If the mean difference is negative and its 95% CI lies wholly to the left of zero, then we can conclude that laser surgery is superior to manual surgery. We will perform sequential testing of the non-inferiority and superiority hypotheses.

Secondary continuous outcomes such as uncorrected distance visual acuity at 12 months, corrected distance visual acuity and patient reported outcome measures Catquest-9SF will be analysed in a similar fashion. The percentage of study eyes experiencing adverse events (e.g. posterior capsule tears, dropped lens) in the two groups will be compared using Fisher’s exact tests.

In addition regression analyses will be performed for continuous outcomes such as corrected distance visual acuity at 12 months for the study eye, adjusting for baseline habitual logMar visual acuity and the randomisation stratifiers (treatment centre, surgeon, and whether or not patients have one or both eyes eligible). Baseline habitual logMar visual acuity is only collected for the study eye and therefore distance visual acuity outcomes for the fellow eye, whether they are unaided or corrected, will only be adjusted for the randomisation stratifiers.

Pearson’s correlation coefficients (or Spearman’s rank correlation coefficients, depending on the distribution of the data) will be used to assess the relationships between the continuous objective and subjective outcome measures.

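### QALYs are adjusted for baseline only on a judgement about the observed data; adjusting for baseline EQ-5DV in every case is more precise and needs no new data

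*Protocol*

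**What the plan says.** Protocol section 5.10.6.1 (Within-trial analysis) builds a utility profile for each patient from EQ-5DV "at baseline and six week, three month, six month and 12 month follow-up time points", with linear change between points. It then states: "Utility estimates will be calculated according to the area under the curve approach", "adjusting for baseline differences in patients in the trial arms if necessary". It does not say what makes adjustment necessary, which baseline variables are meant, or which model is used. Section 5.10.6.3, headed as the health economic analysis plan, sets a Bayesian framework and acceptability curves but does not return to baseline adjustment.

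Three other places bear on the point:

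- Section 5.10.4.2 compares the primary outcome by "regression analysis adjusting for baseline habitual logMar" visual acuity and the stratifiers, with no condition attached. Site is a fixed effect and surgeon a random effect.
- Section 5.9.1.1 allocates by "minimisation with a random element with stratification by a) treatment centre, b) surgeon, and c) whether in the local clinician’s opinion", the patient will need surgery on one or both eyes. Utility is not among the factors.
- Figure 1 in section 5.6 schedules EQ-5DV at the baseline visit. Section 5.4.3 puts surgery typically 4 to 8 weeks after enrolment, and section 5.4 places randomisation on the day of surgery. Baseline EQ-5DV is therefore a pre-randomisation covariate.

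**The concern.** Baseline utility enters the area under the curve directly as its first point. More importantly, it is likely to correlate with every later point. A chance difference between arms at baseline therefore carries through to the QALY difference unless the analysis removes it.

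Under the present wording, removal depends on someone deciding that the arms differ enough. This has two consequences. An imbalance judged unremarkable is left in, and the precision that adjustment would give in every case is obtained only in some. There is also room for discretion. Section 6.13.1 reports clinical and patient-reported outcomes after the 3-month visits and the health economic analysis later, so nothing in the text prevents the choice being made after some comparative results are known.

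The quantities affected are the incremental QALYs, and through them the cost-effectiveness ratio and the acceptability curve.

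**Working it through.** **What the protocol supplies.** It gives no expected QALY difference, utility SD or correlation, so there is no QALY figure to reproduce. Its relevant figures are the arm sizes in section 5.7, and these reproduce closely:

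- 2 × (1.96 + 1.2816)² × 0.32² / 0.1² = 215.2, so 216 per arm (432 in total, as stated).
- 216 × 1.59 = 343.4, so 344 per arm (688 in total, as stated).
- 344 / 0.85 = 404.7, against 404 per arm stated (808 in total).

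I use 404 (all randomised) and 344 (after the planned 15% dropout).

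**Assumptions, not in the documents.** Baseline utility SD 0.25; QALY SD 0.20; baseline-QALY correlation r of 0.3, 0.5 and 0.7. Surgeon clustering is ignored.

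**Step 1: chance baseline difference.** SE = SD × √(2/n).

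- 404 per arm: 0.25 × √(2/404) = 0.0176.
- 344 per arm: 0.25 × √(2/344) = 0.0191.

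**Step 2: carry-over to unadjusted QALYs.** The regression slope of QALY on baseline is r × 0.20/0.25 = 0.8r. The shift from a one-SE imbalance is 0.8r times the SE in step 1.

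**Step 3: scale.** The SE of the unadjusted QALY difference is 0.20 × √(2/404) = 0.0141, or 0.20 × √(2/344) = 0.0153. The shift in step 2 is exactly r times this SE.

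**Step 4: variance.** Let V be the variance of the unadjusted difference.

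- Always adjusting: (1 − r²)V, a saving of r² against never adjusting.
- Adjusting only if baseline p < 0.05 (one possible reading of the condition): the imbalance stays in whenever |z| < 1.96. Its retained share is 0.95 − 2 × 1.96 × φ(1.96) = 0.95 − 0.229 = 0.721, where φ is the standard normal density. The variance is (1 − r² + 0.721r²)V.
- Saving of always against conditional: 0.721r² / (1 − r² + 0.721r²). At r = 0.3 this is 0.0649/0.9749, at r = 0.5 it is 0.180/0.930, and at r = 0.7 it is 0.353/0.863.

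| r | shift, 404 per arm | shift, 344 per arm | shift as share of own SE | variance saved vs never | variance saved vs p < 0.05 rule |
|---|---|---|---|---|---|
| 0.3 | 0.0042 | 0.0046 | 0.3 | 9% | 7% |
| 0.5 | 0.0070 | 0.0076 | 0.5 | 25% | 19% |
| 0.7 | 0.0099 | 0.0107 | 0.7 | 49% | 41% |

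**Step 5: check by simulation under a different set-up.** This used a common utility SD of 0.20 at all five time points, correlation between time points of 0.3/0.5/0.7, 404 per arm, a true difference of zero and 4,000 runs.

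- SD of the QALY difference, never adjusted: 0.0099/0.0111/0.0124.
- Adjusted only if baseline p < 0.05: 0.0096/0.0104/0.0113.
- Always adjusted: 0.0086/0.0081/0.0073.
- Overall rejection rate under the conditional rule: 5.0%/3.7%/2.8%, so not inflated.
- In runs where the baseline statistic lay between 1.5 and 1.96, just short of the trigger: mean shift 0.008/0.012/0.017, and rejection about 10 to 16%.

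The percentage gains differ from the table because these correlations between time points imply baseline-QALY correlations of 0.49/0.67/0.81. The ordering of the three rules is the same.

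**The case against.** The strongest objection is that this is deferred detail. Section 5.10.4.1 promises a full analysis plan, section 5.10.6.1 is written in outline, and the covariates and model for QALYs are ordinary content for such a plan. It stands for the covariate list and the model, whose absence is not a fault here. It does not remove the point, because the protocol is not silent: it states a condition. A later plan that defined the trigger would still leave the adjustment dependent on the data.

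It is also true that the clause speaks of baseline differences in patients and names neither utility nor a test. Utility is the natural reading, since the sentence concerns utility estimates. The p < 0.05 trigger used above is only a working assumption.

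Several stronger readings may tempt a reader, and the documents do not support them:

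- *That the QALY estimate is biased or its error rate inflated.* Under 1:1 randomisation the unadjusted difference is unbiased on average, and the simulated overall rejection rate is at or below 5%. The 10 to 16% applies only to imbalances just short of an assumed trigger.
- *That the ratio will change sign.* No expected QALY difference is given. That it is small is an inference from the non-inferiority design and its assumption of no true acuity difference. The one-SE shift is also below one SE of the QALY difference, so it lies within sampling uncertainty that the acceptability curve already reflects.
- *That the full 9 to 49% is lost under the protocol's wording.* That range compares with never adjusting. A conditional rule recovers part of it.
- *That baseline's place in the curve is the main route.* Its direct trapezoid weight is (6/52)/2 = 0.058. Most of the carry-over comes through correlation with later utilities.

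**Conclusion.** The point holds as a worthwhile improvement to one secondary outcome. Section 5.10.6.1 fixes a data-dependent adjustment rule where an unconditional one is available, is better, and is already used for the primary outcome. The harm is bias conditional on the realised imbalance, lost precision and analyst discretion.

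On the assumed SDs and correlations, the size is a shift of about 0.004 to 0.011 QALY per one-SE imbalance. The variance saving is about 7 to 41% against a p < 0.05 rule. These magnitudes depend on values the protocol does not give, and the second also on how the condition is read. The direction depends on neither, provided baseline and QALY are correlated.

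**What to change.** In section 5.10.6.1, delete the last two words of the adjustment clause. State instead that incremental QALYs will be estimated by regression on arm and baseline EQ-5DV utility, whatever the observed baseline difference. The randomisation stratifiers should be handled as in the primary analysis (site fixed, surgeon random, one or both eyes as a covariate), all within the planned Bayesian analysis. Report the unadjusted result as a sensitivity analysis.

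The cost is a sentence or two of text. Baseline EQ-5DV is already collected, so no new data or visits are needed.

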#### 5.10.6.2 Model based analysis

In the lifetime model, cost-effectiveness will be calculated in terms of the incremental cost per QALY gained. A review of previous cost-effectiveness and cost-utility analyses will be conducted to identify any existing modelling work that may be drawn on for developing the model structure and informing model parameters. The specific details of the data required to populate the model will be determined following the development of the model structure. We will undertake deterministic (one-, two- and multi-way) and probabilistic sensitivity analysis, the latter assuming appropriate distributions and parameter values that will also be used to construct cost-effectiveness acceptability curves.

#### 5.10.6.3 Health Economic Analysis Plan

All analyses will be undertaken within a Bayesian framework. Methods for conducting economic evaluation using clinical trial data will be applied following O’Hagan and Stevens (30) and O’Hagan, Stevens and Montmartin. (31) Monte Carlo simulation methods will be used to construct a cost-effectiveness acceptability curve, based on the expected net benefit statistic, to estimate the probability that the intervention is cost-effective for a range of values of societal willingness to pay per QALY. We will also subject the results to extensive deterministic (one, two, and multi-way) sensitivity analysis.

Cost components included in the analysis will consist of (but not necessarily be limited to) the cost of surgery for both arms of the trial, complications arising from surgery, all relevant diagnostic investigations, revision surgery where necessary, hospital length of stay, outpatient attendances, hospital readmissions, primary care contacts, A&E attendances, and prescribed medications. The volume of resource use for each cost component will be measured directly from trial CRFs. Unit costs will be taken from standard published sources where possible. Where published unit costs are not available site specific unit costs will be obtained as required.

#### 5.10.6.4 Additional analyses – Value of information

No value of information analysis is planned at present.

## 5.11 Data Monitoring

### 5.11.1 Independent Data Monitoring Committee

Further details of the roles and responsibilities of the Independent Data Monitoring Committee (IDMC), including membership, relationships with other committees, decision making processes, and the timing and frequency of interim analyses (and description of stopping rules and/or guidelines where applicable) are described in detail in the **FACT** IDMC Terms of Reference (ToR).

### 5.11.2 Interim Analyses

No formal interim analysis is planned, but reports concerning patient safety and key efficacy outcomes will be prepared for review by the Independent Data Monitoring Committee who may request an interim analysis if a report raises concern.

The IDMC will also be asked to review all the assumptions used for the sample size calculation before the end of recruitment.

### 5.11.3 Data Monitoring for Harm

#### 5.11.3.1 Safety reporting

Definitions of harm of the EU Directive 2001/20/EC Article 2 based on the principles of ICH GCP apply to this trial.

Table 2: Adverse Event Definitions

| **Adverse Event (AE)** | Any untoward medical occurrence in a study participant which does not necessarily have a causal relationship with the treatment under study e.g. abnormal laboratory findings, unfavourable symptoms or diseases. |
| --- | --- |
| **Serious Adverse Event (SAE)** | Any AE that :   - results in death - is life threatening* - requires hospitalisation or prolongs existing hospitalisation** - results in persistent or significant disability or incapacity - is a congenital anomaly or birth defect - or is another important medical condition*** |
| **Suspected Unexpected Serious Adverse Event** | A serious adverse event, the nature or severity of which **is not consistent** with the known potentially **expected** events associated with the applicable trial treatment. The event is evaluated as having a possible, probable or definite relationship to a trial treatment **and** is unexpected for that trial treatment. |
| * the term life threatening here refers to an event in which the patient is at risk of death at the time of the event; it does not refer to an event that might hypothetically cause death if it was more severe (eg a silent myocardial infarction)  ** Hospitalisation is defined as an in-patient admission, regardless of length of stay, even if the hospitalisation is a precautionary measure for continued observation. Hospitalisation for pre-existing conditions (including elective procedures that have not worsened) do not constitute an SAE  *** Medical judgement should be exercised in deciding whether an AE is serious in other situations. | |

Adverse events include:

- an exacerbation of a pre-existing illness
- an increase in the frequency or intensity of a pre-existing episodic event or condition
- a condition (regardless of whether PRESENT prior to the start of the trial) that is DETECTED after surgery. (This does not include pre-existing conditions recorded as such at baseline.)
- continuous persistent disease or a symptom present at baseline that worsens following surgery

Adverse events do NOT include:

- Medical or surgical procedures: the condition that leads to the procedure is the adverse event
- Pre-existing disease or a condition present before treatment that does not worsen
- Hospitalisation where no untoward or unintended response has occurred eg elective cosmetic surgery

#### 5.11.3.3 Other Notifiable Adverse Events

All cases of posterior capsule rupture with vitreous loss including dropped nucleus will be notified to the CCTU and Chief Investigator within 48 hours of the time of surgery.

Any laser errors or faults resulting in non-delivery of the laser to perform the intended steps will be notified to the CCTU and Chief Investigator within 48 hours of the time of surgery.

Any pregnancies during the trial will be notified to the CCTU immediately the site are aware. Patients should continue to attend follow up visits until birth. Patients should be encouraged to attend follow up visits until birth. A pregnancy outcome form must be submitted to CCTU and will be queried if not received within 10 months of the pregnancy being reported.  Failure to send a pregnancy outcome form may result in a triggered on site monitoring visit.

#### 5.11.3.4 Investigator responsibilities relating to safety reporting

All non-serious AEs, whether expected or not, should be recorded in the patient’s medical notes and reported in the toxicity (symptoms) section of the Follow-up Form and sent to CCTU within 4 weeks of the study visit. TSAEs should be notified to CCTU immediately the investigator becomes aware of the event (in no circumstance should this notification take longer than 24 hours).

##### 5.11.3.5.1 Seriousness assessment

When an AE occurs, the investigator responsible for the care of the participant must first assess whether or not the event is serious using the definition given in Table 1. If the event is classified as ‘serious’ then an SAE form must be completed and CCTU notified immediately.

##### 5.11.3.5.2 Severity or grading of Adverse Events

The severity of all AEs (serious and non-serious) in this trial should be graded using the most current version of the Common Terminology Criteria for Adverse Events (CTCAE) of the National Cancer Institute (NCI) (version 4.0, 3, June 2010 at the time of writing this Protocol).

Severity is based on a score between 1 and 5 as follows:

- **Grade 1** - Mild; asymptomatic or mild symptoms; clinical or diagnostic observations only; intervention not indicated.
- **Grade 2** - Moderate; minimal, local or non-invasive intervention indicated; limiting age-appropriate instrumental Activities of Daily Living (ADL).
- **Grade 3** - Severe or medically significant but not immediately life-threatening; hospitalisation or prolongation of hospitalisation indicated; disabling; limiting self-care ADL.
- **Grade 4** - Life-threatening consequences; urgent intervention indicated.
- **Grade 5** - Death related to AE.

